## Abstract

**Background:**

Physical activity has proven to be beneficial for physical functioning, cognition, depression, anxiety, rest-activity rhythm, quality of life (QoL), activities of daily living (ADL) and pain in older people. The aim of this study is to investigate the effect of walking regularly on physical functioning, the progressive cognitive decline, level of depression, anxiety, rest-activity rhythm, QoL, ADL and pain in older people with dementia.

**Methods/design:**

This study is a longitudinal randomized controlled, single blind study. Ambulatory older people with dementia, who are regular visitors of daily care or living in a home for the elderly or nursing home in the Netherlands, will be randomly allocated to the experimental or control condition. Participants of the experimental group make supervised walks of 30 minutes a day, 5 days a week, as part of their daily nursing care. Participants of the control group will come together three times a week for tea or other sedentary activities to control for possible positive effects of social interaction. All dependent variables will be assessed at baseline and after 6 weeks, and 3, 6, 9, 12 and 18 months of intervention.

The dependent variables include neuropsychological tests to assess cognition, physical tests to determine physical functioning, questionnaires to assess ADL, QoL, level of depression and anxiety, actigraphy to assess rest-activity rhythm and pain scales to determine pain levels. Potential moderating variables at baseline are: socio-demographic characteristics, body mass index, subtype of dementia, apolipoprotein E (ApoE) genotype, medication use and comorbidities.

**Discussion:**

This study evaluates the effect of regular walking as a treatment for older people with dementia. The strength of this study is that 1) it has a longitudinal design with multiple repeated measurements, 2) we assess many different health aspects, 3) the intervention is not performed by research staff, but by nursing staff which enables it to become a routine in usual care. Possible limitations of the study are that 1) only active minded institutions are willing to participate creating a selection bias, 2) the drop-out rate will be high in this population, 3) not all participants will be able to perform/understand all tests.

**Trial registration:**

NTR1482

## Background

Aging may coincide with a decline in the level of physical activity [1]. This age-related decline in physical activity is often related to difficulties in physical performances, e.g. walking and getting out of a chair [2,3]. There is ample evidence that in cognitively intact older people living in the community or in long-term care, physical performance can be enhanced by physical activity interventions [4-10]. It is suggested that the intensity of the intervention is positively related to its effectiveness, i.e. a higher intensity produces a higher effect [11]. Nursing home residents are sometimes considered as too frail or too cognitively impaired to benefit from physical activity interventions, but cognitively impaired people seem to benefit from physical activity interventions just as much as cognitively intact people [7]. Furthermore, it has been suggested that frail dependent people only benefit from frequent individualised interventions, while less frail people already respond positively to traditional group interventions [12]. Other studies, including residents with and without cognitive impairment [7,10] or only people with cognitive impairment [11,13-16], confirmed that all residents can improve physical performances through physical activity, but evidence of high-quality studies is still limited or inconclusive.

The risk of dementia might be reduced by physical activity due to its positive effect on cognition [4,17-21], especially on executive functions (EF) [18,21]. When people already show a cognitive decline or suffer from dementia, which highly affects cognition due to neuropathology [22], results on the effects of exercise on cognition are equivocal [13,14]. An explanation for not finding a beneficial cognitive effect was that the interventions mainly consisted of strength-, balance- and/or flexibility-based exercises [14]. A recent meta-analysis indicated that the evidence is not sufficient for firm conclusions about the effectiveness of physical activity interventions on cognition in dementia [23]. The evidence that is available is promising since exercise has a large effect on cognition (Cohen's d = 1.31) and was observed as being significantly different from the control group (moderate effect: Cohen's d = 0.56 and 0.57) [16,24]. More research is warranted, because the available studies differ in exercise protocols, durations and outcome measures [14,23].

One of the risk factors for dementia is an increased level of anxiety and/or depression [25]. In healthy older people physical activity interventions can increase mental health, e.g. self-esteem, happiness and mood [4,26]. Looking explicitly at depression and anxiety, physical activity interventions can reduce the depressive symptoms within 3 months in older people with a depression [27] or anxiety after 3 weeks in people with a chronic physical condition, e.g. fibromyalgia [28]. Long-term effects of exercise on depressive symptoms and anxiety remain to be demonstrated in clinical trials [4,27]. Even though physical activity as a treatment for depression may be as effective as medication, it is currently under-used for this disorder despite having many additional health benefits, for example a reduced risk of heart disease, stroke, high blood pressure, some cancers, type 2 diabetes, osteoporosis and obesity [27]. This makes a physical activity treatment appropriate for older people with a combination of physical and mental health problems such as dementia [27]. In people with dementia evidence of helping with depression is limited [11,23], but the results of available studies are promising [13,14].

Together with a rising level of depression and cognitive impairment, the prevalence and frequency of sleep disorders in long term care residents is increasing [29]. More than half of the residents suffer from some kind of sleep disorder [29]. Night-time wakefulness can lead to increased daytime sleeping and vice versa [30]. Sleep disorders and a lack of activities negatively influence each other [29]. Long-term care residents spend extended periods of time in bed and are sedentary during the daytime, which contributes to abnormal circadian rhythms, i.e. rest-activity rhythm [30]. In older persons with or without dementia, a physical activity intervention seems to be effective [24,31-34], especially in people with poor sleep at baseline [33]. These studies, however, are scarce since the majority of physical activity intervention studies are multi-dimensional, i.e. physical activity is combined with bright light or a decrease in noise at night [24,30,31,33]. Such a combination hampers the understanding of which intervention is (most) effective [35]. A disturbance in the rest-activity rhythm is one of the prominent clinical symptoms in people with dementia which should be recognized and enhanced, since it has a high impact on the quality of life (QoL) [31].

QoL is determined by many aspects in life, e.g. quality and quantity of sleep [36], cognitive functioning [36] and level of depressive symptoms [37]. Exercise programs can slow down the decline in QoL in older community dwelling people [38] and in a combined resident group of people with and without dementia [39]. However, for a group including only people with dementia the evidence for an effect on QoL due to physical activity is limited [11,13,23].

QoL is also affected when people with dementia lose the ability to cope with the physical activities of daily life (ADL), e.g. eating, bathing, using the toilet, dressing, walking and continence [40]. Due to participation in a physical activity intervention, a combined resident group of people with and without dementia can prevent or reduce a decline in ADL compared to a control group [12,39]. In groups with only older people with dementia, there is some evidence that physical activity can improve the ability to cope with ADL [16,41], but there were not sufficient studies for a meta-analysis to conclude whether or not physical activity could be effective for ADL performance in people with dementia [13,23].

The risk to decline in ADL performance increases by approximately 20% for each (additional) painful part of the body, i.e. the neck, back, hands, hips, knees or feet [42]. In older people pain is often caused by the musculoskeletal condition of the joints [43]. In cognitively intact older people a dose-response relationship exists between the level of physical activity and pain; a higher physical activity level was related to less stiff and painful joints [43] and people experienced less pain during a cancer treatment when they performed more aerobic exercises, e.g. walking [44]. In addition, there is more evidence that pain can be reduced by stretching activities [45] or resistance training [46] and specifically (low) back pain by resistance, agility or stretching activities [46]. In contrast, a moderate-intensity endurance and strengthening program had no effect on pain in healthy elderly [45] and neither had a 12 weeks walking program in older people with dementia [47]. No other studies including people with dementia examined the effect of physical activity on pain even though this is necessary since pain is often under-diagnosed and under-treated in people with dementia [48,49].

Studies related to older people with (or without) dementia have not been able to reach a consensus on the types and intensity of the exercise, nor the frequency and duration of the intervention to be most effective and efficient [14]. This is due to the variety in outcome measures; one outcome measure can respond faster to a physical activity intervention than another outcome measure [14]. The effect on outcome measures is also dependent on the age of participants, the cognitive impairment and frailty level [14]. However, in both frail and non-frail older adults regular exercise is the only therapy found to consistently improve health aspects, e.g. physical function, cognitive performance and mood [4]. Most meta-analyses and reviews have concluded that longitudinal randomized controlled trials (RCT) are of vital importance [4,9,10,12-14,18-20,50,51]. Especially people with more severe cognitive impairment should be included in future research [14]. As mentioned above, physical activity has proven to be beneficial to improve or slow down many health aspects in older people with dementia. The aim of the present study is therefore to investigate longitudinally the effect of regular walking on physical functioning, cognition, level of depression and anxiety, rest-activity rhythm, QoL, ADL and pain in older people with dementia.

## Methods/design

### Participants

Participants are older mobile people with dementia who are visiting day care or living in a home for the elderly or nursing home in the Netherlands. Inclusion criteria are 1) a diagnosis of dementia or presence of cognitive impairment that is reported in the medical status and 2) ambulatory with or without walking aid (walker or cane). Exclusion criteria are the presence of personality disorders, cerebral traumata, hydrocephalus, neoplasm, disturbances of consciousness and focal brain disorders.

### Study design and randomization

This study is a RCT. Participants will be randomly divided into the intervention or control group. In order to preclude that the effects arise only from the intensified social contacts during intervention, the control group within a residency will come together three times a week for tea or other sedentary activities, e.g. watching television. The Medical Ethical Committee of VU university medical center approved the study. Oral and written informed consent will be obtained from all participants or their relevant relatives prior to their enrolment.

### Intervention

The intervention consist of a daily 30 minute walk, 5 times a week under supervision of an assistant, e.g. medical staff, volunteers or family members. Depending on the participant, the assistant, the living area and the weather, the intervention can take place in the morning or afternoon, inside or outside, during midweek and/or weekends. Each day the participant has walked will be carefully noted, together with the time of day, duration and whether it was inside or outside.

### Sample size

Sample size calculation was performed using the statistical power analysis program G*Power 3.1 [52] which has the possibility to perform power analyses for a repeated measures design with a between group variable. Based on two meta-analyses studying the effect of physical activity on cognition [16,24], the estimated effect size in this study is expected to be moderate to large (Cohens f = 0.32). Using a type 1 error of 0.05, a power of 0.80, seven repeated measurements and 2 groups, a sample size of 70 in each group is required. Taking into account an attrition rate of 25%, 175 participants should be included in this study.

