## Discussion

This paper presents the design of a RCT, which aims to explore the longitudinal effect of regular walking on several health aspects of older people with dementia. The strength of this study is that 1) the intervention is not performed by the research staff, but by the nursing staff which enables it to become a routine in usual care, 2) we have a high number of repeated measurements, i.e. one baseline and 6 post measurements, 3) the various outcome variables enables us to analyse the development of different health aspects within 18 months.

Possible limitations of this study are that 1) only active minded institutions are willing to participate creating a selection bias, 2) there will be a (high) drop-out rate, for example due to death, 3) not all participants will be able to perform/understand all tests.

This method is appropriate to collect data on the effectiveness and feasibility of a walking program. It is also interesting to examine what aspects determine the compliance of the participants. Due to the aging and dementia process, it is not always necessary to increase in test score to find an effect of the intervention, but stabilizing cognitive and behavioural functioning in those who participate in the walking group would also be worthwhile.

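### The 25% attrition allowance is added to the 140 required instead of divided out, so 175 recruits leave about 131 completers, short of the stated requirement and its power of 0.80

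*Protocol article*

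**What the plan says.** The Sample size section of the protocol article gives every input and the result in consecutive sentences. The effect size is described thus: "the estimated effect size in this study is expected to be moderate to large (Cohens f = 0.32". The other settings are: "Using a type 1 error of 0.05, a power of 0.80, seven repeated measurements and 2 groups". From these the section concludes that "a sample size of 70 in each group is required", which is 140 in total. It then makes the attrition adjustment: "Taking into account an attrition rate of 25%, 175 participants should be included in this study". No inflation formula is shown, and nothing elsewhere in the article revises either number. The Discussion lists attrition among the limitations: "there will be a (high) drop-out rate, for example due to death".

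**The concern.** Three statements stand side by side: 140 participants are needed, 25% will be lost, and 175 are to be recruited. They cannot all be true, because a quarter of 175 is about 44 and the remainder is below 140.

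The target is what the trial recruits to, and the power of 0.80 is what readers take from the section. If the plan's own attrition assumption proves exactly right, the trial still ends below the number it says it needs. That matters more here because follow-up runs to 18 months in an elderly population with dementia, and the article itself expects heavy losses. The target has no margin on the assumption the authors regard as least secure.

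**Working it through.** **Inputs**, all from the Sample size section: type 1 error 0.05; power 0.80; f = 0.32; seven measurements; two groups; 70 per group, so N = 140; attrition d = 0.25; number to include 175.

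**Step 1: reproduce the 175.**
- Adding the percentage to the completers: 140 × (1 + 0.25) = 175. This is exactly the stated figure.
- Dividing by the retained share: 140 / (1 − 0.25) = 186.67, so 187. Per group, 70 / 0.75 = 93.3, so 94 per group or 188 in total.

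The stated figure therefore comes from the first formula. It is 12 to 13 recruits below the second.

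**Step 2: what 175 delivers.**
- Completers at 25% attrition: 175 × 0.75 = 131.25, about 131, or 65 to 66 per group.
- Shortfall: 140 − 131 = 9.
- Attrition at which 175 leaves 140: 1 − 140/175 = 0.20.

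**Step 3: reproduce the 140, so that the shortfall can be put as power.** The article names G*Power 3.1 and a repeated measures design with a between-group factor, but not the procedure. Several readings were tried with f = 0.32 and seven measurements:

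| Procedure | Total N for power 0.80 |
|---|---|
| Between-group main effect, correlation 0.5 | 46 |
| Between-group main effect, correlation 1 (the maximum) | 80 |
| Univariate group-by-time test, sphericity | 26 or fewer |
| Univariate group-by-time test, lower-bound epsilon | 82 |
| Multivariate (MANOVA) group-by-time test, f read as f(V) | 140 |

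Only the last matches. It uses a noncentral F with df1 = 7 − 1 = 6, df2 = N − 7 and noncentrality λ = f² × N.
- N = 139: power 0.798.
- N = 140: λ = 0.1024 × 140 = 14.34, df 6 and 133, power 0.802.

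So 140 is the smallest N that reaches 0.80 under this test.

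**Step 4: power at 131 completers.**
- Same test: λ = 0.1024 × 131 = 13.41, df 6 and 124, power 0.768.
- Without relying on that procedure: take 140 as giving exactly 0.80 and scale the noncentrality by 131/140. Power is then 0.773 for a 1-df test and 0.768 for a 6-df test.

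Both routes give about 0.77.

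**The case against.** The arithmetic is not in dispute. The case on the other side concerns the power figure and how much it matters.

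- **The procedure is inferred.** The article does not say that a MANOVA interaction test was used or that 0.32 is f(V). If 0.32 were applied to the between-group main effect, 131 completers would have power of at least 0.95. That is a fair caution about quoting 0.77 as certain. It does not rescue the plan, because that reading needs at most 80 participants and cannot yield the stated 70 per group.
- **The analysis may use six time points.** The Statistical analysis section labels the repeated measures T1 to T6, whereas the sample size uses seven. With six measurements and the same f(V), power is 0.800 at N = 131 and 0.831 at N = 140. This is correct, but it replaces a stated input. On six measurements the plan's 140 would not be the required number in the first place.
- **Drop-outs may contribute data.** Many who leave will have earlier visits, and an analysis that uses them would lose less power. This stands as a limit on the 0.77. It does not remove the contradiction, since the Sample size section inflates for drop-outs precisely because it counts them as lost.
- **The effect is small.** Nine completers and about three points of power are well within the uncertainty of the assumed effect size and attrition rate, and nothing here biases the estimate or the type 1 error. That is true and bears on how serious the error is, not on whether the sentence is wrong.

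**Conclusion.** The point holds. On the plan's own figures, 175 recruits with 25% attrition leave about 131 completers against 140 required. The correct target is 187 (188 for equal groups), and 175 corresponds to 20% attrition. This part needs no power model.

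The loss of power is modest: from 0.80 to about 0.77, so the type 2 error rises from 20% to about 23%. That figure assumes seven measurements as stated, the test that reproduces the plan's 140 (or a simple calibration of 140 to power 0.80), and no contribution from those who drop out. The stated power does not follow from the plan's own inputs, so the sentence needs correcting.

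**What to change.** Replace the attrition sentence with one of these:

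1. Keep 175 recruits and 25% attrition, and state that about 131 completers are expected, with power of about 0.77.
2. Keep 175 and state that it allows for 20% attrition. Given the drop-out the Discussion expects, the lower rate would need a reason.
3. Keep 25% attrition and power 0.80, and set the target at 187, or 188 for equal groups.

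Whichever is chosen, name the G*Power procedure and the effect-size definition so that the 140 can be checked. If the analysis will be a mixed model using all available visits, restate the power for that model.

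Options 1 and 2 cost one sentence, with a slightly less favourable power or a lower tolerated attrition, and no extra participants. Option 3 costs 12 to 13 more recruits.

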### Recruitment

Participants for this study will be recruited via medical staff of aged care facilities. First, the medical staff will be informed about the goal and procedure of the study. Secondly, possible participants will be selected within subunits of the institutions by a team, including the researcher, medical staff and nurses. Third, an information letter with informed consent will be sent to the legal representatives of the participants, together with an invitation to attend an oral presentation. Fourth, once written consent is received, subunits make a schedule for assistants to accompany the regular walks of participants in the intervention group.

### Procedure

The outcome variables are measured at baseline (pre-treatment: T0), after 6 weeks of intervention (post-treatment: T1) and after 3 (T2), 6 (T3), 9 (T4), 12 (T5) and 18 (T6) months of intervention. Trained experimenters, blinded to the intervention assignment, will administer the neuropsychological tests, physical tests and level of depression, anxiety and pain. The nursing staff fills in questionnaires to measure QoL, ADL and define the stage of dementia. The other variables are objective measurements.

### Characteristics

Characteristics include *age*, *gender*, *subtype of dementia, type of living situation*, i.e. independently in society, in a home for the elderly or in a nursing home as well as the following aspects:

#### Highest education level

The highest education level will be determined on a seven-point scale with 1 = less than elementary school, 2 = 6 grades of elementary school, 3 = 7 or 8 grades of elementary school, 4 = 3 years of lower general secondary education, 5 = 4 years of lower general secondary education, 6 = pre-university education and higher vocational education, 7 = university and technical college [53].

#### Body mass index (BMI)

BMI is calculated as weight in kilograms divided by height in meters squared.

#### Apolipoprotein E (ApoE) genotype

ApoE type 4 allele (ApoE4) plays a major role in cerebral perfusion and metabolism and is a known risk factor for late onset Alzheimer's disease (AD) [54]. In addition, ApoE4 carriers show different effects on cognition as a result of some therapy than non-carriers [55,56]. In view of this possible moderating effect on treatment outcome, ApoE genotype of participants will be determined. Buccal swabs will be taken by making use of Catch-all™ collection swabs (Epicentre, Madison, Wisc., USA). First, participants must rinse their mouth thoroughly with water. Then two swabs are taken from each participant, will be left to dry for approximately 30 minutes and are frozen until DNA will be released from the swab by a rapid lysis technique [57] and the nucleotide sequence will be determined [58].

